**Figure 4 figure4:**
[figure not shown]
Examples of SMARTFAMILY app screens. A. Detailed status of activity goal achievement; B. Manual activity recording; C. Food recordings; D. Manual food recording; E. Start screen with overview of goal achievement.

### Features of the SF2.0 App

Table 1 provides an overview of the behavior change techniques incorporated in the SF app and the additional behavior change techniques of SF2.0 (Figure 5), allocated to the basic psychological needs [47].

Figure 5 shows examples of the SF2.0 app screens. While SF focuses on elementary functions, SF2.0 includes a more comprehensive range of app features such as JITAIs [58] and an interactive, humanized goal-setting coach who interacts with the app user in a personal way, providing hints and facts to achieve a higher app (and therefore, health behavior) commitment (ie, gamification). In both apps, triggered and app-based ecological momentary assessment (EMA) [59] is used. Supplementary to EMA of physical activity and healthy eating in SF, EMA was extended in SF2.0 by the real-time measurement of behavioral and affective correlates of physical activity and fruit and vegetable intake, including current mood, stress, and exhaustion (see #14-16 in Figure 5) as additional control variables [54,55]. This assessment is prompted at least 4 times a day, paralleling inactivity prompts (see below). Inactivity-triggered prompts are sent when the participant is inactive for at least 60 minutes (neither <2 sensor values at >2 MET nor 100 steps). Push notifications regarding inactivity are inhibited for the remaining day if the participant reaches at least 60 minutes of moderate-to-vigorous physical activity on the respective day. Every evening at 7 PM, participants are asked if they recorded all the necessary manual information of physical activity and healthy eating. The last assessment of mood, exhaustion, and stress occurs when the participant presses the “going-to-sleep button” (if there has not been an inactivity trigger during the last 60 minutes). Sleep quality is assessed every morning after the participant pushes the “get-up button” in the app. Furthermore, EMA is used to evaluate the reasons for inactivity (see #18 in Figure 5).

To further increase motivation, SF2.0 comprises a more detailed gradation of goal achievement. Participants can gather stars for every 10% of goal achievement. If the family achieves their individual goal during 1 intervention week, they are instructed to set a higher goal for the next week. In SF2.0, the interactive goal-setting coach advises them about a promising goal for the following week. If the family does not achieve its individual goal, the coach instructs family members to set the same or even a slightly lower goal for the next week. For recording of the different parameters and operation principles of SF2.0, see SF. One additional feature included in SF2.0 is adapted from the SMARTACT Toolbox [53-55]. Here, users are instructed to take a picture of every single meal (including snacks), producing an exact timestamp of food consumption (Figure 5, #25). Furthermore, SF2.0 comprises a real-time assessment of mood, exhaustion, and stress (Figure 5, #14-16), a gamification approach (visualized by the personal coach and collectable stars; Figure 5, #1), an inactivity-triggered ecological momentary intervention (Figure 5, #17,18), and a provision of up to 5 health-related facts by the interactive coach to improve health literacy [60]. These additional features are related to the inclusion of further behavior change techniques as shown in Table 1.

**Table 1 table1:** Implementation of the basic psychological needs and behavior change techniques within the app features.

Self-determination theory, basic psychological needs	Autonomy	Relatedness	Competence
SF^a^ app features and number of behavior change techniques (Michie et al [37])	Self-imposed weekly goal-setting (eg, steps, duration of moderate-to-vigorous activity, fruit/vegetable intake) (behavioral goal-setting, #5^b^) App displays current status on performance and goal achievement (prompt review of behavioral goals, #10, prompt self-monitoring of behavior, #16, provide feedback on performance, #19) Calendar displays overview on performance (provide feedback on performance)	App implemented in a family-based setting, encouraging social support (plan social support/social change, #29) and identification as a role model (prompt identification as role model/position advocate, #30)	Set slightly higher weekly goals than current performance (set graded tasks, #9); rewards are provided according to progressively set goals via motivation notifications (shaping, #14) Motivation notifications at a level of 25%, 50%, 75%, and 100% of goal achievement (prompt rewards contingent on effort or progress toward behavior; provide rewards contingent on successful behavior, #12, #13)
Additional app features in SF2.0	Includes all the features of the SF app.	Additional review of the common goals via daily notifications in the morning (prompt review of behavioral goals, #10)	Interactive goal-setting coach provides knowledge about physical activity and healthy eating (provide information on consequences of behavior in general, #1) Gathering stars when achieving goals for each 10% of goal achievement (prompt rewards contingent on effort or progress toward behavior; provide rewards contingent on successful behavior, #12, #13) Inactivity-based reminders for physical activity according to ecological momentary intervention principles (teach to use prompts/cues, #23) Ecological momentary assessment of sleep, mood, exhaustion, and stress (barrier identification/problem solving, #8)

^a^SF: SMART*FAMILY*.

^b^These numbers refer to the Behavior Change Techniques (BCTs) shown in Michie et al [37].

**Figure 5 figure5:**
[figure not shown]
Examples of SMARTFAMILY2.0 app screens. A. Detailed status of activity goal achievement; B. Manual activity recording; C. Nutritional goal achievement; D. Manual food recording; E. Morning screen with an overview of the status quo and remaining physical activity and fruit and vegetable intake until goal achievement; F. Ecological momentary assessment and ecological momentary intervention; G. Just-in-time adaptive intervention. EMA: ecological momentary assessment; EMI: ecological momentary intervention; JITAI: just-in-time adaptive intervention; FVI: fruit and vegetable intake.

### Outcomes

All self-reported measures and diaries are implemented in German language.

#### Primary Outcomes

Primary outcome measures are device-based measured physical activity (ie, amount of steps taken, minutes of moderate-to-vigorous physical activity) via accelerometers (T_0_ and T_1_) as well as self-reported assessed physical activity levels via questionnaires (T_0_-T_2_) and diary records (T_0_ and T_1_). Furthermore, healthy eating (fruit and vegetable intake) is assessed via questionnaires (T_0_-T_2_) and diary records (T_0_ and T_1_). Primary outcomes are similar for SF and SF2.0.

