### Participant Recruitment

Participants are recruited in schools, school holiday programs, music schools, and sports clubs via personal communication, newspapers, and email distribution lists of the Karlsruhe Institute of Technology. Power analyses for analysis of covariance with 2 groups and 4 covariates using G*Power [52] yields a total of 52 families with approximately N=156 participants (assuming 3 family members), to find a small-to-medium effect (α=.05, 1-β=.80, Cohen *f*=0.25). In order to increase power and to compensate for potential dropouts, we aim for a total of 60 families per trial. Please see Figure 3 for the planned participant flow for SF and SF2.0.

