#### Self-reported Physical Activity (Questionnaire and Diary)

Self-reported physical activity is measured using valid and reliable measures. In the SF trial, the International Physical Activity Questionnaire [63] was used at all 3 measurement points for adults [64]. For children, the 60-minute screening measure for moderate-to-vigorous physical activity is used. These measures were chosen in order to account for the requirements of different age groups. However, due to better comparability of results, an adapted version (referring to the activities of the last week and not of a typical week) of the General Physical Activity Questionnaire [65] is used in SF2.0 for children and adults. In both trials, all participants complete a diary complementary to accelerometers [66], indicating time and type of activity, duration and intensity on each single day of the measurement week, and if this activity is carried out as a family or alone.

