#### Fruit and Vegetable Intake (Questionnaire and Diary)

Fruit and vegetable intake is assessed using a single item asking for the total amount of fruits and vegetables consumed within a typical week [67] in the questionnaire as well as using a description in a diary of detailed food consumption during 1 week by indicating the time of the meal, ingredients, portions of fruit and vegetable intake, and whether the meal was consumed within the family or alone.

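### SF and SF2.0 each name six unranked primary measures, power one test at .05 and state no rule across outcomes

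*Protocol article*

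**What the plan says.** The Primary Outcomes section begins: "Primary outcome measures are device-based measured physical activity (ie, amount of steps taken, minutes of moderate-to-vigorous physical activity) via accelerometers". It continues "as well as self-reported assessed physical activity levels via questionnaires", together with diary records, and then "Furthermore, healthy eating (fruit and vegetable intake) is assessed via questionnaires", again with diary records. Accelerometer and diary data are collected at T0 and T1, and questionnaires at T0, T1 and T2. The list is said to be similar for SF and SF2.0. The measures are not ranked, and none is marked as the main one.

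The Participant Recruitment section reports one power calculation, for an analysis of covariance with two groups and four covariates, "to find a small-to-medium effect (α=.05, 1-β=.80, Cohen" *f* = 0.25). It gives 52 families, or about 156 people, and does not name the outcome. The target is 60 families per trial.

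The Data Analysis section applies one form of group-by-time model to device-based and self-reported outcomes. It mentions Tukey-corrected post hoc tests and a rule that main effects are considered only after a significant interaction.

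Two instrument details also matter. The intake questionnaire is "a single item asking for the total amount of fruits and vegetables consumed within a typical week", whereas the SF2.0 activity questionnaire was adapted to ask about the past week: "referring to the activities of the last week and not of a typical week". In SF, adults answered the International Physical Activity Questionnaire. "For children, the 60-minute screening measure for moderate-to-vigorous physical activity is used".

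**The concern.** With six measures of equal standing and no statement of what counts as success, any one favourable result can be reported as a positive primary finding. Neither safeguard in the Data Analysis section prevents this: the Tukey correction concerns post hoc comparisons, and the interaction rule works inside a single model.

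The risk is not spread evenly over the six. Under Randomization and Blinding, intervention families are told about the mHealth nature of the study and controls are told only of an epidemiologic assessment. Four of the six measures are self-reports and so are the most open to expectation and reporting effects. A trial could claim success on one of them while both accelerometer measures show nothing.

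**Working it through.** **Count.** Two accelerometer measures (steps, MVPA minutes), two activity self-reports (questionnaire, diary) and two intake self-reports (questionnaire, diary): 2 + 2 + 2 = 6 per trial.

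**The plan's own sample size.** Inputs from Participant Recruitment: f = 0.25, alpha .05, power .80, 2 groups, 4 covariates. Method: noncentral F with λ = f²N and denominator df = N − 2 − 4.
- Numerator df 1, the literal reading for two groups: N = 128. At N = 156, λ = 0.0625 × 156 = 9.75 and power is 0.87.
- Numerator df 2, as for a group-by-time effect over three occasions: N = 158, close to the stated 156. At N = 156 power is 0.80.

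The article does not give the numerator df, so both are carried below. On either reading the calculation covers one test at .05.

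**Chance of at least one false-positive primary result**, six tests at .05, no true effects:
- Independent: 1 − 0.95⁶ = 1 − 0.735 = 0.265.
- Simulated equicorrelated two-sided tests. The correlations are assumptions, because the article gives none:

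| Correlation | 0.2 | 0.3 | 0.5 | 0.7 | 0.9 |
|---|---|---|---|---|---|
| Probability | 0.25 | 0.24 | 0.21 | 0.16 | 0.11 |

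Even at 0.9 the figure is about twice the nominal level.

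**Power per outcome if alpha is shared**, N = 156, f = 0.25, people treated as independent:

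| Alpha per test | Numerator df 1 | Numerator df 2 |
|---|---|---|
| .05 | 0.87 | 0.80 |
| .025 (two primaries) | 0.80 | 0.71 |
| .05/6 = .0083 (six primaries) | 0.67 | 0.56 |

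The .025 row is the stricter Holm step; once one of the two is significant, the other is tested at .05.

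Correlation within families lowers these values. The article gives no intraclass correlation. For three members per family the design effect is 1 + 2 × ICC. Dividing λ by it, at alpha .025 and numerator df 1, gives power 0.72, 0.65 and 0.58 for assumed ICCs of 0.1, 0.2 and 0.3.

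**Intake item.** The questionnaire asks about a typical week. At T1 this is three weeks of intervention after baseline, so the answer may partly describe eating before the app. At T1 a one-week diary is also collected. At T2 the questionnaire is the only intake measure in the primary list.

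**Activity questionnaire.** SF uses different instruments for adults and children, and the Data Analysis section does not say how they are combined or separated. SF2.0 uses one instrument for both.

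**The case against.** Three objections carry weight. First, .05 appears only in the power calculation. The article sets no significance level for the outcome tests, and a separate analysis plan might adjust for multiplicity. That is fair, and the error rates above are therefore conditional. But the number and equal rank of the primary measures are set in this article, and so is a sample size for one undivided test. A later correction over six would cost power that was not planned for.

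Second, a reader might infer that two of the questionnaire measures cannot be analysed or interpreted at all. The documents do not support that. A typical-week item can be analysed; its weakness is a recall window that may dilute change, and the diary covers T1. The two-instrument issue is confined to SF, and the article never states that the two scores are pooled. Separate analysis would fit its stated reason for using different instruments, which was the needs of different age groups.

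Third, a reader might add the effect of unmodelled family clustering and arrive at a much larger error rate. That is a separate issue, and its size would depend on an intraclass correlation that the article does not give. It does not belong in the multiplicity figure.

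Which measures should be primary is also the sponsor's decision. Diary intake is itself an unblinded self-report, so it is only an example below.

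**Conclusion.** The concern holds for both trials in this form: six unranked primary measures, one power calculation at an undivided .05, and no rule linking the outcomes to a conclusion. If each is tested at .05, the chance of at least one false-positive primary result per trial is about 26% under independence and 21 to 25% at assumed correlations of 0.5 to 0.2.

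The recall window of the intake item (mainly at T2) and the two activity instruments (SF only) are subsidiary. They weaken particular measures and make neither trial unanalysable.

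**What to change.** Before any outcome analysis by group, state for each trial:

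1. **One primary measure per domain at T1**, the post-intervention occasion at which all six are collected. For example, accelerometer MVPA or steps for activity and diary fruit and vegetable intake for eating. The sponsor chooses.
2. **Holm across the two at an overall .05**, with the remaining four measures made secondary.
3. **The typical-week intake item kept as a labelled supportive measure.** It should not be reworded for families already enrolled: different wordings at T0 and at T1 or T2 within one person would be confounded with change over time, and a version flag would not remove that.
4. **In SF, separate analyses of the adult and child activity questionnaires.**

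This needs text only. SF data collection has ended, so there only the analysis can change; SF2.0 is still collecting data. The cost is that four measures lose primary status and power per outcome is lower. At N = 156 with people treated as independent it is about 0.80 at .025 with numerator df 1, or 0.71 with df 2, and less once family clustering is allowed for. Keeping all six with a Bonferroni split would cost more (0.67 or 0.56).

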#### Device-Based Measured Physical Activity (Accelerometers)

Hip-worn accelerometers (Move 3/Move 4) are used to continuously record physical activity (3-axial acceleration, which is conveyed by algorithms into steps, time spent during moderate [3-6 MET]/vigorous [>6 MET] physical activity and sedentary time [1-1.5 MET]). The accelerometers are connected via Bluetooth low energy with the smartphone app to provide users direct feedback on their physical activity levels. The accelerometer’s validity was tested in previous studies and is considered accurate for assessing physical activity [61,62]. Participants are instructed to wear the accelerometer during wake time and remove it only for taking a shower, swimming, or during certain sports involving bodily contact to minimize the risk of injuries. This nonuse time is added manually into the app. Device-based activity assessment takes place at T_0_ and T_1_.

#### Self-reported Physical Activity (Questionnaire and Diary)

Self-reported physical activity is measured using valid and reliable measures. In the SF trial, the International Physical Activity Questionnaire [63] was used at all 3 measurement points for adults [64]. For children, the 60-minute screening measure for moderate-to-vigorous physical activity is used. These measures were chosen in order to account for the requirements of different age groups. However, due to better comparability of results, an adapted version (referring to the activities of the last week and not of a typical week) of the General Physical Activity Questionnaire [65] is used in SF2.0 for children and adults. In both trials, all participants complete a diary complementary to accelerometers [66], indicating time and type of activity, duration and intensity on each single day of the measurement week, and if this activity is carried out as a family or alone.

#### Fruit and Vegetable Intake (Questionnaire and Diary)

Fruit and vegetable intake is assessed using a single item asking for the total amount of fruits and vegetables consumed within a typical week [67] in the questionnaire as well as using a description in a diary of detailed food consumption during 1 week by indicating the time of the meal, ingredients, portions of fruit and vegetable intake, and whether the meal was consumed within the family or alone.

#### Secondary Outcomes

##### Demographics

In the T_0_ questionnaire, demographic information of the participants is collected, including sex, age, height, weight, highest education level, and tobacco and alcohol use (parents, only in SF), and attended school level (children). Moreover, participants are asked to rate their perceived general health [68]. The remaining questions are kept consistent over the 3 measurement points and are similar for SF and SF2.0.

##### Intrinsic Motivation Toward Physical Activity

To assess activity-related intrinsic motivation, the Behavioral Regulation in Exercise Questionnaire [69] is used [70].

##### Intrinsic Motivation Toward Healthy Eating

For assessing dietary-related intrinsic motivation, the Regulation of Eating Behavior Scale [71] is used.

##### Self-efficacy for Physical Activity and Healthy Eating

Activity-related self-efficacy and dietary-related self-efficacy are assessed using the health specific self-efficacy scale [72].

##### Family Health Climate

The family health climate is assessed using the family health climate scale [73].

#### Additional Outcome Measures of SF2.0

##### Intention to Participate

The intention to participate in physical activity and to eat healthy is assessed by a single-item measure [74,75]. Additionally, these measures were adapted to capture the participants’ intention to use smartphone apps for the promotion of physical activity and healthy eating.

##### Additional Measures in SF2.0

Healthy eating is assessed as fulfilment of the 10 guidelines of the German Nutrition Society [76] using the respective items of the Food Frequency Questionnaire [77,78] and diary information. Within the intervention, time and frequency of (shared) meals can be analyzed using timestamps of pictures taken [54]. Additionally, *adherence and user engagement* within the intervention are controlled for in SF2.0 by using app usage data stored on a server at the University of Konstanz (see Figure 2). Hence, app usage data (eg, recording of fruit and vegetable intake, achievement of physical activity and fruit and vegetable intake–related goals), and device-based measured physical activity are analyzed.

### Data Analysis

First, the baseline characteristics of the study population are summarized within each cluster randomized group on individual and family levels for all measures to control for group differences. Then, all primary outcome data will be screened for normal distribution by using the Shapiro-Wilk test. Data will be checked for outliers. To further analyze changes in health behavior, mixed-model analysis of covariance with time (T_0_ and T_1_ for device-based physical activity; T_0_, T_1_, and T_2_ for self-reported physical activity and healthy eating) as within-subjects and group (intervention group vs control group) as between-subjects factor will be conducted, with covariates being family health climate, self-efficacy, and intrinsic motivation (Behavioral Regulation in Exercise Questionnaire and Regulation of Eating Behavior Scale) as well as intention in SF2.0. Results of the Mauchly test will be checked for homoscedasticity of data and results will be corrected accordingly (ε>0.75 Huynh-Feldt, ε<0.75 Greenhouse-Geisser). Furthermore, homogeneity of the error variances will be checked, as assessed by Levene test. If this test does not reveal significance, a Box-Cox transformation will be applied to the data. Moreover, Tukey-corrected posthoc tests will be considered for detailed interpretation of results. Main effects will only be considered if the interaction is found to be significant. All analyses will be conducted using SPSS 26 statistical software (IBM Corp).

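### The primary model uses the T0 outcome only as a level of the time factor, so its two-occasion tests are change-score comparisons without baseline-outcome adjustment, which costs precision

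*Protocol article*

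**What the plan says.** The Primary Outcomes section gives every primary measure a T0 value. It begins "Primary outcome measures are device-based measured physical activity (ie, amount of steps taken, minutes of moderate-to-vigorous physical activity) via accelerometers (T_0_ and T_1" and goes on to activity and fruit and vegetable questionnaires (T0 to T2) and diaries (T0 and T1).

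The Data Analysis section then fixes the model:

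- **Time:** "mixed-model analysis of covariance with time (T_0_ and T_1_ for device-based physical activity; T_0_, T_1_, and T_2_ for self-reported physical activity and healthy eating") is the within-subjects factor.
- **Group:** "group (intervention group vs control group) as between-subjects factor will be conducted".
- **Covariates:** "with covariates being family health climate, self-efficacy, and intrinsic motivation (Behavioral Regulation in Exercise Questionnaire and Regulation of Eating Behavior Scale) as well as intention". The last of these applies only to the second trial, so there are four scales in SF and five in SF2.0.
- **Test that decides:** "Main effects will only be considered if the interaction is found to be significant".
- **Model family:** "Results of the Mauchly test will be checked for homoscedasticity of data and results will be corrected accordingly", with Huynh-Feldt or Greenhouse-Geisser factors. This is classical repeated-measures analysis.

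The Participant Recruitment section sizes the trial by "Power analyses for analysis of covariance with 2 groups and 4 covariates using G*Power". That count matches the four SF scales. Baseline measures are to be summarised by arm, but nothing carries the baseline outcome into the model as a covariate, and nothing constrains the arms to a common T0 mean.

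**The concern.** The T0 value of an outcome is usually among the best predictors of its T1 value. When T0 enters as a response, the coefficient on baseline is fixed at 1. When it enters as a covariate, the coefficient is estimated from the data. Two things follow whenever the T0-T1 correlation is below 1:

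- **Precision.** The change-score contrast has the larger residual variance. One-week diaries or one week of steps may be only moderately correlated between weeks, and the loss is then material.
- **Chance imbalance.** Families are allocated by simple randomisation, with about 26 to 30 per arm if allocation is 1:1. An arm that happens to start low tends to drift back up, and the change score counts that drift as intervention effect. An arm that starts high is penalised.

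**Working it through.** **Inputs.** From Participant Recruitment: f=0.25 (d=2f=0.5 for two equal groups), alpha .05, power .80, 52 families, about 156 people at three per family. Assumed, because the article does not give them: 1:1 allocation (78 people per arm), two-sided testing, the T0-T1 correlation rho, and the intra-family correlation (ICC).

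**The plan's own figure.** A covariance-analysis power calculation (noncentral F, noncentrality N × f², numerator df 1, two groups, four covariates) gives N=128 for 80% power, not 156. At N=156 its power is 87.3%. That mismatch is a separate matter; 156 is used below because it is the stated size.

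**Step 1: what the planned test is.** With two occasions, the group-by-time term (with covariate-by-time terms in the model) is the group term in a regression of T1 − T0 on group and the same covariates. On one simulated data set (n=156, four covariates):

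| Analysis | F for group effect |
|---|---|
| Repeated-measures group × time | 4.6115 |
| T1 − T0 on group and covariates | 4.6115 |
| T1 on group, covariates and T0 | 6.302 |

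The first two are identical. With three occasions the interaction has 2 df, so the identity holds for the T0-T1 and T0-T2 contrasts, not for the omnibus test.

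**Step 2: residual variance**, in units of the outcome variance and before the other covariates:

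- change score: 2(1 − rho)
- T0 as covariate: 1 − rho²
- ratio: 2/(1 + rho), which is 1.54 at rho 0.3, 1.33 at 0.5, 1.18 at 0.7 and 1.11 at 0.8

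**Step 3: power** (noncentral t, d=0.5, N=156). The standard error is √(variance × 2/78). At rho 0.5 that is √(1.00 × 2/78) = 0.160 against √(0.75 × 2/78) = 0.139. For the clustered columns the variance is multiplied by 1 + 2 × ICC = 1.6 (assumed ICC 0.3, three per family) and df are counted on families.

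| rho | Independent: change | Independent: T0-adjusted | ICC 0.3: change | ICC 0.3: T0-adjusted |
|---|---|---|---|---|
| 0.3 | 74.6% | 90.2% | 53.4% | 71.8% |
| 0.5 | 87.3% | 94.8% | 67.8% | 79.8% |
| 0.7 | 98.0% | 99.1% | 87.8% | 92.4% |
| 0.8 | 99.8% | 99.9% | 96.9% | 98.1% |

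**Step 4: chance imbalance.** The SD of the between-arm T0 difference is √(2/78) = 0.16 outcome SD if members are independent, and √(2 × 1.6/78) = 0.20 at ICC 0.3. The change-score estimate moves by −(1 − rho) per unit of imbalance. For a one-SD imbalance the shift is:

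- rho 0.5: 0.5 × 0.16 = 0.08 to 0.5 × 0.20 = 0.10, or 16% to 20% of d=0.5
- rho 0.7: 0.3 × 0.16 = 0.05 to 0.3 × 0.20 = 0.06, or about 10% to 12%

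**Step 5: do the psychosocial covariates make up the loss?** No. In simulation under no effect at rho 0.5, with a covariate explaining 0, 20 or 40% of outcome variance, the variance ratio was 1.32, 1.45 and 1.70. The slope of the change-score estimate on imbalance was −0.50, −0.62 and −0.84. With T0 as covariate the slope was about 0. Both estimators averaged about 0 over all runs.

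**The case against.** The strongest reply is that a group-by-time repeated-measures test is standard and valid, and fits the stated interest in change and its maintenance. That stands. A reader might infer that the planned test is biased, or is an unadjusted change-score comparison. Neither follows: it is unbiased on average under sound randomisation, and it adjusts for four or five scales. Nor does calling it an analysis of covariance contradict anything, since that name does not require the baseline outcome among the covariates.

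Second, the gain rests on an assumed rho. This also stands. With independent members the gain at N=156 is 7.4 points at rho 0.5, but about 1 point at 0.7 and 0.1 at 0.8. At the recruitment target of 60 families (180 people at three each, before dropout) it is 5.5 points at rho 0.5 and 0.6 at 0.7. A gain near 10 points at rho 0.5 with independent members appears only at N=128, which is not the plan's number.

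Third, the Randomization and Blinding section has families allocated before they are recruited, and tells the two arms different things about the study. Either could produce systematic T0 differences. A reader might infer that conditioning on T0 removes any baseline difference; it removes the error from chance imbalance only. This limits the claim and makes a change-score sensitivity analysis necessary. It does not make the model without T0 adjustment the better primary choice in a randomised trial.

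**Conclusion.** The point holds as one of efficiency and conditional accuracy, not validity. The article states the model and its covariates explicitly, so this is a choice it makes and not a detail left to a fuller document. The equivalence to a change-score test is exact for accelerometry and diaries, and for the T0-T1 and T0-T2 contrasts of the questionnaires.

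The loss is substantial if rho is about 0.3 to 0.5 (15.6 to 7.4 points of power at N=156 with independent members) and close to nil at 0.7 to 0.8. It is larger if family members' outcomes are correlated: 12.0 points at rho 0.5 and 4.6 at rho 0.7 with an assumed ICC of 0.3. These figures rest on d=0.5, equal arms, three members per family and the variance before psychosocial adjustment. The change is worth making because T0 adjustment has the lower large-sample variance at any rho below 1 and the T0 data are already collected.

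**What to change.** In the Data Analysis section, for SF2.0 before its analysis and for SF if it has not yet been analysed:

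- Make the primary analysis of each outcome a model of T1 on group, with the person's own T0 value of that outcome as covariate and a family random effect.
- For the three-occasion questionnaires, model T1 and T2 together, adding visit, visit-by-group and visit-by-T0.
- Report the adjusted group difference at T1 as the effect.
- Keep the time-by-group result as a sensitivity analysis, to show how far the conclusion depends on baseline differences that may not be due to chance.

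The cost is revised analysis wording and syntax, one or two degrees of freedom for the T0 terms, and an effect reported as an adjusted difference instead of an interaction F test. No extra participants or visits are needed. Data acquisition for SF has ended, so a change there should be dated and described as made after data collection.
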